### The trial: data collection and outcome measures

Data will be collected for both groups on a face-to-face basis in the person’s home. This will include standardised questionnaires used to record demographic information, relevant clinical data, social and practical needs and the nature and extent of social networks. Relevant outcome measures will be identified following Phase 0, but some of the kinds of measures that are likely to be used are outlined below.

People living with illness may be asked to complete (with help) measures such as: (i) The FACIT-PAL-14 [27]; (ii) The UCLA 3-item loneliness scale [28]; (iii) The eight-item modified Medical Outcomes Study Social Support Survey (mMOS-SS) [29]; (iv) Items regarding community and generalised trust, cohesion and social inclusion from Lewis’s Social Capital Questionnaire [30] and a measure of social and/or practical need and social network. Carers engaged in the study may complete measures such as: (i) the 11-item Duke Social Support Index [31]; and (ii) the American Medical Association Carer Self-Support Survey [32].

Measures will be completed at T0 (baseline), T1 (4 weeks) and T2 (8 weeks) as recommended by Greene [33]. The place of care over time, use of paid and unpaid resources and unplanned health service utilisation will also be recorded at each time period. The researcher will read out the questionnaires to the person and show potential responses on large print, laminated A4 flash cards to aid those with any visual impairment.

### Process evaluation

A ‘mini’ process evaluation will also be nested within the INSPIRE trial and conducted at the end of the study, when a small, but diverse, number of patients, carer and volunteers will be invited to take part in a one-to-one interview to explore their experience and views of the new intervention and the process of its implementation. In addition, the time taken to obtain informed consent and collect data, exclusions, recruitment and drop-out rates (patients, their family and volunteers) and missing data will be recorded and reported throughout the course of the RCT.

### Ethical approval

An application for ethical approval was submitted to the Mid-West University Hospitals Scientific Research Ethics Committee in September 2014 and was approved in November 2014.

### Data analysis

#### Phase 0

Qualitative data from interviews and focus groups will be transcribed, anonymised and entered into MAXQDA for standard thematic analysis. Other qualitative analytical techniques (e.g., grounded theory) will also be considered.

#### Phase I: implementation and pilot testing of compassionate communities volunteer training

Descriptive and inferential statistics with specific pre- and post- training comparisons and utilising appropriate tests to assess any change over time in death anxiety and confidence in communication.

#### Phase 2: exploratory (parallel group) RCT

Trial data will be cleaned, checked for coding errors and entered into SPSS for analysis. Differences between the control and intervention groups at baseline will be examined. Given that studies, such as that proposed here, can be subject to attrition and missing data [33], we will endeavour to utilise the recommendation from MOREcare [34] to manage these issues should they arise in this study (e.g. examining patterns of missing data and utilising a taxonomy of attrition). The primary endpoint will be change in unmet social and/or practical needs in the intention-to-treat sample. Secondary efficacy endpoints have also been described. Other end-points include death and the person requesting withdrawal from the study.

It is likely that an analysis of covariance (ANCOVA) for the primary endpoint and for secondary endpoints will be conducted, supplemented by a repeated measures analysis. However, at this stage, given the lack of certainty around the total sample size (and its distribution), it is perhaps appropriate to highlight that the method of analysis will involve fitting between group, repeated measures models with two levels of treatment variable (intervention group, control group) and three time points (T0, T1, T2) to the primary and secondary outcome measures. Model assumptions will be checked and where there is evidence of non-normal distribution, outcomes will be transformed, for example by dichotomising or categorising data. Auxiliary analyses will assess the interaction of potential modifiers (for e.g., age, sex, size of social network at baseline) with treatment in the models.

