**Design:**

The INSPIRE study will be conducted within the Medical Research Council (MRC) Framework for the Evaluation of Complex Interventions (Phases 0–2) and includes an exploratory two-arm delayed intervention randomised controlled trial. Eighty patients and/or their carers will be randomly allocated to one of two groups: (I) Intervention: GNP in addition to standard care or (II) Control: Standard Care. Recipients of the GNP will be asked for their views on participating in both the study and the intervention. Quantitative and qualitative data will be gathered from both groups over eight weeks through face-to-face interviews which will be conducted before, during and after the intervention. The primary outcome is the effect of the intervention on social and practical need. Secondary outcomes are quality of life, loneliness, social support, social capital, unscheduled health service utilisation, caregiver burden, adverse impacts, and satisfaction with intervention. Volunteers engaged in the GNP will also be assessed in terms of their death anxiety, death self efficacy, self-reported knowledge and confidence with eleven skills considered necessary to be effective GNP volunteers.

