### Randomisation

Randomisation will be conducted independently (and after the baseline interview) by a statistician, using the minimisation method [23]. This method will yield an equal balance between groups by level of assessed social and/or practical need and social network. This method ensures a balanced distribution of potentially prognostic factors, even in small trials [24]. The control group will be monitored for contamination by the intervention at the eight week interview where a question will be included asking participants in the control group if they have had contact with anyone who have received or volunteered as part of the intervention.

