### Sample size

It is anticipated that up to 80 people will be recruited to the INSPIRE trial. The trial is intended as a pilot, to test procedures for acceptability, estimate the likely rates of recruitment and retention of the participants, and permit calculation of appropriate sample sizes based on the primary outcome measure for future larger scale studies. Given the exploratory nature of the trial, we estimate that the proposed sample size of 80 is a realistic estimate based on the nature of the intervention and the possible size of the study population, as well as what is feasible within the one year timeframe for the nature of the Phase II element under the MRC Framework. A sample of 80 is also larger than that used in a similar study using a delayed intervention RCT design to determine the effectiveness of a new palliative care service [25]. Furthermore, as the precise choice of outcome measure depends on the findings from Phase 0 of the study, it is not possible at this stage to conduct a power analysis. However, when we have identified the primary outcome measure, we will be in a better position to estimate sample size based on the expected difference on the outcome measure between the control and intervention group, from use of the measure with a similar population. This study has three units of analysis: (1) the person living with life limiting illness; (2) the carer and (3) the volunteers.

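### The only remedies named for non-normal outcomes, dichotomising and categorising, change the endpoint, do not fit the planned models and usually cost precision

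*Protocol article*

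**What the plan says.** The relevant text is in the protocol article, Data analysis, Phase 2. The primary endpoint is the change in unmet need, analysed by intention to treat. ANCOVA is described as likely. Between-group repeated-measures models over the three time points are to be fitted to primary and secondary outcomes. Assumptions will then be checked, and "where there is evidence of non-normal distribution, outcomes will be transformed, for example by dichotomising or categorising data". No other remedy is named.

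Three other statements bear on this:

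- **Size.** "It is anticipated that up to 80 people will be recruited to the INSPIRE trial" (Sample size). The abstract describes them this way: "Eighty patients and/or their carers will be randomly allocated to one of two groups".
- **Measure and power.** The Sample size section says that "it is not possible at this stage to conduct a power analysis", because "the precise choice of outcome measure depends on the findings from Phase 0 of the study". One stated purpose of the pilot is to "permit calculation of appropriate sample sizes based on the primary outcome measure for future larger scale studies".
- **Candidate outcomes.** The data collection section lists possible measures, including a three-item loneliness scale, and says that "use of paid and unpaid resources and unplanned health service utilisation will also be recorded at each time period".

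**The concern.** A variable cut into two or three levels is no closer to normal than the one it replaces. The remedy therefore does not repair the assumption that triggered it. It does change what is estimated: a mean change in need becomes the proportion beyond some threshold, or a shift between bands. That quantity calls for a logistic or ordinal model, not the ANCOVA and repeated-measures models just specified.

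Because the trigger is the observed distribution, the form of the primary endpoint depends on the trial data. In a trial of at most 80 people, the likely price is precision. A further risk arises if the cut-point is also left open, since choosing among cuts inflates the type I error.

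Short scales and service-use counts are often discrete and skewed, so the rule could well be triggered for some secondary outcomes. Whether it would be for the primary cannot be known, because its measure has not been chosen and a change score need not share the skew of the raw score.

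**Working it through.** **Inputs.** N is at most 80. On allocation the Randomisation section says "This method will yield an equal balance between groups by level of assessed social and/or practical need and social network". I take this as 40 per arm, though no ratio is given as a number. The plan has no power calculation, so there is no figure of its own to reproduce. Assumed throughout: two-sided 5% level, no dropout and, except in step 6, no baseline adjustment.

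**1. Binary split of a normal outcome.** Relative efficiency is φ(z_p)² / [p(1 − p)], where p is the share on one side of the cut.

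| Split | Efficiency | Loss | 80 people count as |
|---|---|---|---|
| 50/50 | 0.637 | 36% | 51 |
| 30/70 | 0.576 | 42% | 46 |
| 25/75 | 0.539 | 46% | 43 |
| 20/80 | 0.490 | 51% | 39 |
| 10/90 | 0.342 | 66% | 27 |

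**2. Several ordered categories, normal outcome.** For k equal-sized categories, analysed as ordered, efficiency is k × Σ[φ(c_i) − φ(c_{i+1})]². This gives 0.793 for k = 3, 0.861 for k = 4 and 0.897 for k = 5, so losses of 21%, 14% and 10%.

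**3. What this means at 40 per arm.** Kept continuous, the difference detectable with 80% power is (1.960 + 0.842) × √(2/40) = 0.63 SD. After a median split it is 0.626/√0.637 = 0.79 SD, and after a 25/75 split 0.626/√0.539 = 0.85 SD. Power at 0.63 SD falls from 80% to 60% (50/50), 52% (25/75) or 48% (20/80). With fewer patients the drop from continuous to median split is similar: 71% to 50% at 32 per arm, and 65% to 45% at 28 per arm.

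**4. Non-normal outcomes, where the rule actually applies.** For a scale effect, the efficiency of a split at c against a test of raw means is [c f(c)]² × CV² / [p(1 − p)].

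- Exponential (CV = 1), median split: (0.693 × 0.5)² / 0.25 = 0.48, a loss of 52%. Splitting off the upper quarter gives 0.64, a loss of 36%.
- Log-normal, median split against raw means: 0.72 at log-SD 0.5 (loss 28%), 0.85 at 0.75 (loss 15%), 1.09 at 1.0 (no loss).
- The same log-normal data against a log-scale analysis: 0.637 at the median and 0.539 at 25/75, so losses of 36% and 46%.
- Laplace, location shift, median split against the t-test: 4 f(m)² σ² = 4 × 0.25 × 2 = 2.0, so the split is the better of the two.

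**5. Simulation without baseline adjustment (10,000 runs, 40 per arm).** The t-test kept its size: 4.8% for exponential data and 5.2% for negative binomial data with mean 3 and size parameter 1.5.

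| Setting | t-test | Mann-Whitney | Median split |
|---|---|---|---|
| Exponential, mean ratio 0.55 | 73% | 62% | 43% |
| Negative binomial, means 3 and 1.6 | 73% | 65% | 53% |

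Taking the best of three cuts (at the quartiles) gave type I error of 15% (normal), 14% (exponential) and 13% (negative binomial).

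**6. Simulation with baseline adjustment.** Gamma-Poisson counts with a shared frailty, control mean 4, 40 per arm, 2,000 runs. ANCOVA had type I error of 5.0% (4.6% with HC3 errors). Power for a 40% reduction was 65–67% with ANCOVA and 40–43% after a median split. For a 30% reduction it was 38–39% and 22–24%. With control means varied from 2 to 8, ANCOVA kept its size at about 4–5% and beat the median split in every setting tried, for example 63% against 40% and 88% against 50%.

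**The case against.** The case on the other side is substantial.

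- **The wording is permissive.** The stated remedy is transformation, with cutting as the example. A reader might infer that non-normal outcomes are bound to be dichotomised. The text does not say so, and a log or rank transformation stays open. What stands is that no better remedy is named.
- **The efficiency figures are normal-theory.** A reader might infer that a third to a half of the information is always lost. Steps 2 and 4 show otherwise: several ordered categories lose less, and under strong log-normal skew or heavy tails a median split can match or beat a raw-scale t-test. But log-scale, rank or robust methods handle those cases without cutting.
- **Cut-point timing.** A reader might infer that the cut will be picked after the data are seen. The article only omits a cut-point, and an analysis plan that is not shown could fix one. The 13–15% error rate is therefore conditional.
- **Planning the later trial.** A reader might infer that cutting deprives the pilot of the mean and SD needed for Phase III. It does not, because the rule governs the analysis and raw summaries by arm can still be reported.
- **The simulation inputs are assumptions.** No need count is specified, and the 80 are patients and/or carers, so 40 patients per arm may be optimistic.
- **This is a pilot.** It has no power calculation, and the analysis is worded as provisional. That lowers the weight of lost power, although the Phase II section also sets out to assess effectiveness.

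**Conclusion.** The point holds in limited form. The document names a poor method; it does not merely leave one to the analysis plan. The change of endpoint and the mismatch with the planned models follow from the text and need no assumption about the distribution.

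The cost in precision does need one. It is 36% to 51% for a binary split between 50/50 and 80/20 of a roughly normal outcome, and about 10% to 21% for three to five ordered categories. For skewed outcomes it ranges from about half to none. In the skewed-count settings simulated at 40 per arm, linear analysis on the original scale held its type I error near 5%, so cutting was not needed to protect validity there, and it cost power.

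This is worth correcting before analysis, but it is not a critical defect, given the exploratory aim and the provisional wording.

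**What to change.** Replace the sentence with wording such as:

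> Model residuals will be checked. Where they are clearly non-normal, the outcome stays on its original scale and the baseline-adjusted treatment difference is reported with bootstrap or heteroscedasticity-robust confidence intervals (cluster-robust by participant for repeated measures), with a log or rank analysis as sensitivity. Outcomes that are counts or short ordinal scales use a count or ordinal model. A dichotomised or categorised version is supplementary only, at a cut-point fixed before the outcome data are examined.

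The specific count or ordinal model can be named once Phase 0 has settled the measures. The change needs no new data. It costs a little more analysis work, and a mean difference on a skewed scale is slightly less intuitive than a percentage; the supplementary version can supply that.

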#### Phase 2: experience and impact of engaging as a volunteer

Descriptive and inferential statistics with specific pre- and post–intervention comparisons using appropriate statistical tests (sample size dependent) to determine any changes in the community volunteers with regard to death self-efficacy (as measured by The Death Self-Efficacy Scale [35], fear of death (as measured by The Revised Collett-Lester Fear of Death and Dying Scale [36] and self-reported confidence with the eleven skills considered important for their role.

### Process evaluation

All qualitative data will be transcribed, anonymised and entered into MAXQDA in preparation for analysis. A number of qualitative analytical techniques will be considered, such as grounded theory or Framework analysis.

## Discussion

It is anticipated that the findings from the various elements of the INSPIRE study will represent an invaluable addition to international literature and provide important insights into the effectiveness, efficacy, utility and acceptability of a unique model of social and practical care for people with life-limiting illness. This will help to inform the development of similar models in other jurisdictions and potentially provide the basis for a larger full-scale RCT into the future. If the INSPIRE trial shows that volunteer-led models of social care and practical support are effective, it could provide evidence to show that a relatively low cost intervention can be offered routinely with support from specialist palliative care and primary healthcare providers.
